#### Leadership

Leadership is assessed with items from the questionnaires on Integrative Leadership (FIF, *Fragebogen zur Integrativen Führung*) and Leader-Member-Exchange (LMX-7).

The FIF questionnaire [30, 31] focuses on six dimensions of transformational leadership (fostering innovation, team spirit development, performance development, individuality focus, providing a vision, being a role model), two dimensions of transactional leadership (goal setting, management by exception) (module a: items 1–32) [32] and on laissez-faire and destructive leadership (module d: items 65–68) [33]. All items are answered on a 5-point Likert scale. Physicians with leadership responsibilities will assess themselves, whereas other practice physicians and practice assistants will evaluate their leaders. The instrument allows for a comparison of answers provided by leaders and other personnel.

The LMX-7 measures the relationship quality between employees and supervisors (leaders) [34, 35]. It consists of 7 items with 5-point Likert scales. The LMX values are added to a “sum-score. A high score reflects a positive assessment of the quality of the relationship with the supervisor. Again, practice owners will assess themselves, while employed practice physicians and practice assistants assess their leaders:
General health is assessed using a brief burnout assessment, the World Health Organization-Five Well-Being Index (WHO-5) and the Work Ability Index (WAI).Burnout is measured using two items from the Maslach Burnout Inventory (emotional exhaustion: “I feel burned out from my work”, depersonalization: “I have become more callous toward people since I took this job”) [36]. This brief measure of burnout was shown to provide sufficient information on the likelihood of high burnout among physicians and medical students [37, 38]. The score ranges from 0 = never to 6 = every day, and the raw values are processed to obtain a score for emotional exhaustion and depersonalization, which can be compared to the results obtained by the full Maslach Burnout Inventory [38].Current well-being during the last – 14 days is assessed using the WHO-5 (1998 version) [34, 39]. It consists of 5 items with 6-point Likert scales (5 = all of the time to 0 = at no time). The scores are added to a sum-score ranging from 0 to 25 and are then multiplied by 4 to give the final score, with 0 denoting the worst and 100 representing the best imaginable wellbeing [34].Work ability is measured using a single item of the WAI: “personal prognosis of work ability two years from now” on a 3-point Likert scale [40, 41].Work behavior is assessed using short versions of the Occupational Self-Efficacy Scale (BSW, *Berufliche Selbstwirksamkeit*) and the Work-related Behaviour and Experience Patterns questionnaire (AVEM-44).Self-efficacy is measured using a short version of the BSW [42]. The instrument consists of 8 items with 6-point Likert scales.The interplay between work, personality and health is assessed using the short version of the AVEM-44 [43–46]. The AVEM addresses three aspects, which are particularly important for coping with occupational challenges. It consists of 44 items across three domains: professional commitment (20 items across five scales: subjective importance of work; professional ambition; willingness to work to exhaustion; striving for perfection; distancing ability); coping capacity (12 items across three scales: tendency to resign in the face of failure; proactive problem-solving; inner calm and balance); subjective wellbeing (12 items across three scales, experience of success at work; satisfaction with life; experience of social support). Each scale consists of four items, which are measured on a 5-point Likert scale. AVEM identifies four patterns which describe coping strategies for occupational stress: healthy-ambitious (pattern G), unambitious (pattern S), excessively ambitious (risk pattern A) and burnout (risk pattern B).Chronic stress is measured using the German short version of the Screening Scale of the Trier Inventory for the Assessment of Chronic Stress (TICS-SSCS) [47, 48]. This instrument retrospectively measures strain due to chronic stress, for 3 months. It consists of 12 items on 5-point Likert scales (0 = “never” and 4 = “very often”). The TICS-SSCS values are added to a sum-score. The score ranges from 0 to 48 with 0 denoting “never stressed” and 48 “very often stressed”, and reflects subjective strain due to chronic stress.Occupational health and safety is measured using questions from previous studies [49–52], physicians with leadership responsibilities will answer 29 items on occupational safety culture as reported by the practice owners; other staff will answer 28 items.Individual coping strategies are assessed using 26 items specifying various option for stress prevention, e.g. playing an instrument, going for a walk or hiking outdoors and support from friends. Items were derived from previous studies [10].Various issues relating to work organisation will be addressed, e.g. estimated duration and peaks of waiting times for private and non-private patients, working overtime due to problems with organisational workflows, reasons for waiting times.Team activities and roles will be addressed by requesting the frequencies of team sessions and other team activities. Also participants are asked to self-assess their typical personal team role from a choice of nine options.

Socio-demographic characteristics and practice characteristics will be collected as moderating variables. Stable co-variables (e.g. socio-demographic characteristics of study participants, work-related experience and behavioural patterns (AVEM) [53], practice characteristics) will be collected only at baseline, while changeable variables will be measured at both at baseline and follow up. Study nurses will offer an optional workplace safety sheet at baseline, to be completed together with the practice leader. The sheet addresses issues such as hygiene, emergency exits and skin protection instructions. Participation is voluntary for the leaders; a copy of the report will be provided immediately. For an overall schedule see Fig. 2a.

**Fig. 2 Fig2:**
[figure not shown]
**a** Overall schedule and time commitment for trial participants within the IMPROVEjob intervention. b Summative evaluation: description of outcomes. COPSOQ, Copenhagen Psychosocial Questionnaire; FIF, Integrative Leadership; LMX-7, Leader-Member-Exchange; WHO-5, Health Organization-Five Well-Being Index; WAI, Work Ability Index; BSW, Occupational Self-Efficacy Scale; AVEM-44, Work-related Behaviour and Experience Patterns questionnaire; TICS-SSCS, Trier Inventory for the Assessment of Chronic Stress

### Intervention

The multimodal participatory intervention was initiated by a general practice physician and researcher ([name]). The intervention was designed cooperatively by researchers from the fields of general practice and family medicine and those from occupational medicine, psychosomatic medicine, operations practice research and workplace health promotion. The intervention focuses on the areas of leadership, work processes and work organization, communication, occupational health and safety and workplace health promotion. It is composed of three elements.

#### IMPROVE*job* workshops

The intervention begins with a series of three workshops each lasting 4 h. The three workshops will be held within 1 month with 2-week intervals in between. About 5–6 practices will take part in each workshop depending on the number of staff in each practice. This allows for about 8–10 physicians and 15–25 practice assistants per workshop series. All workshops include presentations by the research team and interactive elements with self-reflection and peer group exchanges.

The specific contents of the workshop are as follows:
Workshop 1 for physicians with leadership responsibilities (practice owners and employed physicians with leadership responsibilities): this executive workshop addresses the topics “role of the executive”, “leadership styles” and “relational leadership competence” including “transactional and transformational leadership”. The workshop includes theoretical inputs delivered via visual presentation, small group interactions, and a skills training session. The later training is designed to allow for training in leadership aspects in a simulated practice scenario with a simulated practice assistant: one participant is asked to take on the role of a physician leader who is facing a conflict between team members with leadership responsibilities. The workshop offers leaders the opportunity to reflect on their own leadership role and values, to increase the awareness for and impact of stress prevention for all team members, and to learn different leadership styles. In particular, different aspects of the relational, transactional and transformational leadership approaches and their effects on employees´ health and team-building are addressed.Workshop 2 for physicians with leadership responsibilities and all practice employees: This workshop addresses issues relating to the communication between practice personnel and patients. Using a theoretical framework and interactive skills sessions with trained simulation patients, participants will learn how to analyse encounters with patients that they perceive as challenging and how to better communicate in such situations. Training in challenging situations is provided by drawing on typical scenarios in primary care practices.Workshop 3 for physicians with leadership responsibilities and all practice employees: this workshop addresses issues relating to “work organisation including appointment scheduling”, “occupational health and safety” and “workplace health promotion”. At the end of the workshop series, practices will be empowered and supported with implementation aids such that they are able to adjust their daily routines according to self-selected goals. Practices will be encouraged to set targets for their implementation phase.

#### IMPROVE*job* toolbox

The toolbox includes materials presented in the workshops and supplemental material. It comprises two booklets (one for physicians with leadership responsibilities and one for practice employees), a desk calendar and a personal code allowing access to a secured web space with additional material for downloading.
The “management logbook” (for physicians with leadership responsibilities): this folder contains material for workshops 1–3 plus supplements.The “employee logbook” provides materials for workshops 2 and 3 plus supplemental material.The desk calendar for practice teams presents a variety of issues from the workshops in a concise card format, e.g. advice on communication with so-called “difficult patients”, on occupational health and safety, and on issues of individual health promotion such as relaxation and ergonomics.Supplemental material for download, e.g. practice checklists and other tools, will be provided via a secured webspace. The personalised access allows for the evaluation of webspace use on an individual level.

#### IMPROVE*job* facilitators

The facilitators are trained members of the research team who will accompany the practices during the change processes by on-site meetings in the practice and/or by phone. Prior to the workshops, the facilitators will be trained in change processes, the setting of GP practices and qualitative data collection in two training sessions. The facilitators concentrate on processes and developments within the practices, but they do not engage in active coaching. They are conceptualised as process companions who remind the practice teams of the project and support the implementation of the intervention. In addition, the facilitators will collect qualitative data in the practices to analyse the relevance, feasibility and implementation of the intervention. The facilitators will take part in the intervention workshops where they will meet the study participants. Also, they will note the practice goals set by each participating practice. After the workshops the facilitators will offer practices to contact them regularly, e.g. once a month, to facilitate the implementation.

### Control group

This study will use a waiting-list control approach. After completion of the follow-up data collection, practices in the control group will be offered the same IMPROVE*job* workshops as practices in the intervention group, including access to the toolbox. The project duration and funding does not allow for IMPROVE*job* facilitators to be involved in the waiting list control group.

### Sample size calculation

The primary hypothesis of this study is that the IMPROVE*job* intervention will have an effect on job satisfaction among personnel working in general practices. The null and alternative hypotheses to be tested are:
$$ {\mathrm{H}}_0:{\upmu}_{\mathrm{I}}={\upmu}_{\mathrm{C}} $$$$ {\mathrm{H}}_{\mathrm{A}}:{\upmu}_{\mathrm{I}}\ne {\upmu}_{\mathrm{C}}, $$

where μ_I_ and μ_C_ denote the mean score difference on the COPSOQ job satisfaction scale between baseline and after 9 months, in the intervention arm and in the control arm.

We aim for power of (at least) 80% with a two-sided significance level α = 0.05. The calculations will be carried out by means of the clustered *t* test [54, 55], assuming an intra-cluster correlation coefficient (ICC) of 0.05 [56]. All power analyses will be made using the software PASS 13, option “Tests for Two Means in a Cluster-Randomized Design”.

Assuming a mean value plus/minus standard deviation for the primary endpoint of 73.6 ± 15 points [57], we calculate that a sample size of 52 clusters (26 practices per arm), each with 3 participating staff members per practice, will be sufficient to detect a change of 10% (7.3 points) with power of 81% at the chosen significance level. With 4 participants per practice, the power will increase to 89%.

Conversely, with 52 practices and 4 participants per practice, the study would have power of 80% to detect a change of 0.43 SD in the primary endpoint (and 0.39 SD with 5 participants per practice). This is comparable to the “minimally important difference” (MID) of 0.4 SD proposed as a relevant change in the COPSOQ job satisfaction score [58]. As the values and standard deviation are lower on this scale for physicians than for practice assistants [57, 59], the sample size calculation is rather conservative. Assuming two practice drop-outs in each of the two groups (intervention and control), we will include physicians and practice assistants from 56 general practices in the study.

### Data management, statistical analyses and steering committee

Data management will be carried out by the ZKSE according to standardised procedures as defined in current standard operating procedures (SOPs). The data management system used by the ZKSE has an integrated audit trail and is Good Clinical Practice (GCP)-compliant. Data will be entered by appropriately trained data-entry staff who are familiar with the study specifics. Double data-entry will be used to ensure data quality. Issues of missing data will be addressed by imputation methods according to standard [60]. All personal data will be kept confidential in an access-restricted database. All analyses will be performed using pseudonymised data. The pseudonymised data will be stored at the ZKSE and the Institute of General Practice and Family Medicine of the University of Bonn. The latter institute will manage access to the data set.

Regarding the primary outcome, we hypothesise that the participatory IMPROVE*job* intervention will improve job satisfaction among practice personnel. A before-and-after comparison between the intervention and the control group will be used for the evaluation. To control for response shift with respect to job satisfaction, a “then-test” will be applied using a separate sheet to be filled after collection of the follow-up questionnaires [61]. For the statistical analysis, the COPSOQ scales will be transformed according to instrument-specific algorithms [27]. The confirmatory analysis to measure the effect of the intervention will be carried out as an intention-to-treat analysis, i.e. all participants who completed the job satisfaction scale at baseline and follow up will be included. The primary analysis will be conducted using a linear mixed model adjusted for clustering and the randomisation strata. Per protocol, the analysis will be performed with the data on physicians with leadership responsibility who took part in the management workshop and in at least one of the two team workshops, and with data on practice assistants who took part in at least one team workshop. Additional analyses will focus on secondary outcomes and on associations between various independent and dependent variables. All analyses will respect the cluster-randomised nature of the study design including approaches for analysis of team aspects within the practices. All measures of the summative evaluation will compare mean differences between follow up and baseline (Fig. 2b).

The project is supported by a steering committee with scientists from various fields (general practice and family medicine, occupational psychology, sociology) and representatives of organisations relevant for transfer and dissemination (statutory health insurance, regional medical association, association for health service and welfare work, regional chamber of industry and commerce).

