### Participants and recruitment

The study will be conducted in general practices of the North Rhine region in Germany. Urban and rural medical practices are selected to ensure better generalisation of the results. Practices will be drawn as random samples from an official list of registered general practice physicians of the Association of Statutory Health Insurance Physicians of North Rhine (in German, *Kassenärztliche Vereinigung Nordrhein*) in these selected areas and from a list of teaching practices of regional universities. We previously showed that teaching practices are typically easier to recruit and do not differ from non-teaching practices with regard to health service characteristics [25]. We therefore aimed for an approximately equal distribution of teaching and non-teaching practices in the final sample.

The practices will be contacted by the Institute of General Practice and Family Medicine of the University of Bonn. Depending on available contact details, practices will be sent invitation letters by mail, fax and/or email, each of which include participant information and an informed consent form for the practice owner. Practices will then be contacted by phone to provide additional study information. As soon as the practice owner has given written consent, a visit by a study nurse from the Center for Clinical Trials in Essen (in German, *ZKSE, Zentrum für klinische Studien Essen*), is scheduled. During this visit, the study nurse will obtain informed consent from each participating team member, distribute and collect the baseline questionnaire data, and complete an observational occupational health and safety form. In the consent form, participants are informed that they are free to discontinue study participation at any time. Questionnaires will be checked for completeness of data. To promote participant retention and to prevent loss to follow up, each participant will receive 50€ after the intervention. In addition, IMPROVE*job* facilitators will motivate participants to complete the study.

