### Randomisation

General practices will be randomised by means of several random lists. These lists include single and group practices and teaching and non-teaching practices, to achieve a roughly equal distribution in both the intervention and the control groups. We chose the stratification factor of (a) single/group practice, because structural characteristic, leadership responsibilities and indicators of psychological wellbeing may differ between practice types [10, 16] and (b) teaching/non-teaching practice, as this factor may influence the motivation to participate in the intervention (and may indirectly influence its effects). The randomisation list is generated by an employee of the ZKSE who is not involved in the selection of the practices. Practices will be randomised after baseline data collection, to ensure that study nurses are blinded for the first site visit. The randomisation allocation will be transferred to scientists at the Institute of General Practice and Family Medicine in written form, who will inform the practices by phone and letter. Blinding of the scientists and the practice personnel is not possible due to the participatory concept of the intervention, which includes workshops. Data analysts will follow a predefined protocol for analysis to avoid bias.

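### The confirmatory analysis is labelled intention-to-treat but defined as a complete-case set, and its relation to the promised imputation is left unstated

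*Protocol article*

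**What the plan says.** All references are to the protocol article.

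- **Analysis set** (Data management, statistical analyses and steering committee): the confirmatory analysis is an "intention-to-treat analysis, i.e. all participants who completed the job satisfaction scale at baseline and follow up will be included".
- **Missing data** (same section, in the paragraph on data handling): "Issues of missing data will be addressed by imputation methods according to standard". No outcome, and no level (item, scale or participant), is named.
- **Model** (same section): "The primary analysis will be conducted using a linear mixed model adjusted for clustering and the randomisation strata". The hypotheses under Sample size calculation concern the mean change in score from baseline to 9 months.
- **Timing and blinding** (Randomisation): "Practices will be randomised after baseline data collection", and "Blinding of the scientists and the practice personnel is not possible".
- **Retention** (Participants and recruitment): "facilitators will motivate participants to complete the study", and each participant is paid 50€. Under Control group, project time and funding do not permit "facilitators to be involved in the waiting list control group".
- **Allowance for loss** (Sample size calculation): "Assuming two practice drop-outs in each of the two groups (intervention and control"), which raises the target from 52 to 56 practices. No allowance for individual staff is stated.

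**The concern.** Intention-to-treat normally means that everyone randomised is analysed in the allocated arm. Here the entry rule requires a completed follow-up scale, which is an event after randomisation. Baseline is collected before allocation, so the people removed are mainly randomised staff whose follow-up is missing.

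The article's own Background section links persistently low job satisfaction to burnout and early retirement, so leaving a practice or not returning the questionnaire may well be related to the outcome. Staff know their arm, the outcome is self-reported, and one retention measure exists in one arm only. If loss is related to both outcome and arm, the completer contrast is no longer protected by randomisation, yet it would be reported as intention-to-treat.

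The imputation sentence does not settle the matter. A participant without a follow-up score cannot be both imputed and excluded from the same analysis, and two analysts could follow this section to different primary results.

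**Working it through.** **1. The plan's own figures.** Inputs from Sample size calculation: SD 15, ICC 0.05, 26 practices per arm, 3 or 4 staff per practice, difference 7.3 points, two-sided 0.05. For a clustered t test, SE = SD × √(2 × [1 + (m − 1) × ICC] / (k × m)), with 2 × (26 − 1) = 50 degrees of freedom.

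- m = 3: SE = 15 × √(2 × 1.10 / 78) = 2.52, power 81.1% (stated: 81%).
- m = 4: SE = 15 × √(2 × 1.15 / 104) = 2.23, power 89.4% (stated: 89%).

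The power figures reproduce, so the sample size calculation is not at fault on its own inputs. The relevant-change benchmark of 0.4 SD is 0.4 × 15 = 6 points.

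**2. Who is excluded.** Baseline precedes randomisation, and entry requires baseline and follow-up scores. The rule therefore acts mainly on the follow-up score. The mixed model does not change this: it could use a person with a baseline score only, but the rule keeps that person out. If the outcome is a change score, such a person contributes nothing in any case.

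**3. Bias of the completer contrast.** Let d be the share lost in an arm and g the mean change of completers minus that of leavers. The mean over everyone is the completer mean minus d × g. So the completer contrast (intervention minus control) differs from the contrast in everyone by

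bias = d_I × g_I − d_C × g_C.

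The documents give no individual loss rate and no gap, so every d and g below is an assumption.

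| Loss, intervention / control | Gap, intervention / control | Bias (points) | Share of 6 points |
|---|---|---|---|
| 20% / 20% | 10 / 10 | 0.20 × 10 − 0.20 × 10 = 0 | 0% |
| 15% / 25% | 5 / 5 | 0.15 × 5 − 0.25 × 5 = −0.5 | 8% |
| 15% / 25% | 10 / 10 | 0.15 × 10 − 0.25 × 10 = −1.0 | 17% |
| 25% / 15% | 5 / 5 | 0.25 × 5 − 0.15 × 5 = +0.5 | 8% |
| 25% / 15% | 10 / 10 | 0.25 × 10 − 0.15 × 10 = +1.0 | 17% |
| 20% / 20% | 5 / 0 | 0.20 × 5 − 0.20 × 0 = +1.0 | 17% |

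A negative sign understates the benefit. The last row shows that equal loss alone does not guarantee zero bias; the gaps must be equal too. For scale, gaps of 5 and 10 points are 5/15 = 0.33 SD and 10/15 = 0.67 SD. The larger one exceeds the 6-point benchmark itself.

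**The case against.** Several counter-arguments are sound and limit the point.

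- **Imputation.** A reader might infer that the completer rule flatly contradicts the imputation sentence. The text does not support that. Imputation may be meant for single items in returned questionnaires (the primary scale has several items), or for the many other scales and covariates. Both sentences can then stand. What remains is that the article does not say which is meant.
- **The label in context.** The per-protocol set is defined by workshop attendance. Against that, intention-to-treat here means inclusion regardless of attendance, so the plan does guard against exclusion for non-adherence. Missing follow-up stays uncovered.
- **Direction.** A reader might infer that the completer analysis inflates the effect. The one arm-specific retention measure, the facilitators, would if anything reduce loss in the intervention arm. With leavers doing worse, that biases against the intervention.
- **Shared incentives.** The payment is not described as arm-specific, and control practices are offered the workshops only after follow-up, which gives them a reason to stay. Differential loss is therefore possible, not established.
- **Practice drop-out.** A reader might count the planned loss of 4 of 56 practices (7%) as evidence of bias. It is assumed equal in the two arms and already budgeted for. With equal gaps it contributes none.
- **Remedy.** A mixed model or multiple imputation assumes data missing at random and removes only bias explained by observed data. With a single follow-up, people with baseline only add little information. This stands, and it is why a delta-adjusted analysis is needed as well.

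None of this changes the definition. It is a sentence in the article, not a detail left to an analysis plan.

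**Conclusion.** The point holds in limited form. As defined, the confirmatory set is complete-case and excludes randomised staff without a follow-up score, so the intention-to-treat label is not accurate. Whether imputation reaches the missing follow-up score is unstated. This rests on the text alone and needs no assumption.

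That the result will be biased is not shown. With a leaver-completer gap of 5 to 10 points in both arms and a 10-percentage-point difference in loss, the bias is 0.5 to 1.0 point in absolute value, or 8% to 17% of the 6-point benchmark. It understates the benefit if control loses more and overstates it if the intervention arm does. It is zero with equal loss and equal gaps. Because this sentence governs the confirmatory test, it should be put right before the follow-up data are analysed.

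**What to change.** 1. Define the confirmatory set as all consenting participants with baseline data in randomised practices, analysed in the arm to which the practice was allocated.
2. Fit a mixed model with baseline and follow-up scores as outcomes, with random effects for practice and person. Alternatively, use multilevel multiple imputation based on baseline score, role, strata, arm and other baseline predictors.
3. State what the imputation covers: single items, the missing follow-up score, other outcomes, or a named combination.
4. Keep the present analysis, relabelled as a complete-case sensitivity analysis.
5. Add a delta-adjusted sensitivity analysis in which the unobserved change of leavers is made progressively worse, separately by arm, because the methods in step 2 assume data missing at random.

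**Cost:** a little more analysis work and possibly a slightly wider confidence interval; no new data. On timing, the article says the trial is ongoing with recruitment completed on 4 March 2020. It does not say whether any follow-up analysis has begun, so the change should be dated and made before the follow-up data are analysed.

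### The primary contrast is on change in job satisfaction, and the baseline score is not named as a covariate: valid, but less precise than a baseline-adjusted model at no saving

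*Protocol article*

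**What the plan says.** Protocol article, 'Sample size calculation': the hypotheses compare two means that "denote the mean score difference on the COPSOQ job satisfaction scale between baseline and after 9 months", one for each arm. The contrast is therefore on change.

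Protocol article, 'Data management, statistical analyses and steering committee': the evaluation is a before-and-after comparison between arms, and "All measures of the summative evaluation will compare mean differences between follow up and baseline". On the model: "The primary analysis will be conducted using a linear mixed model adjusted for clustering and the randomisation strata". The section does not say whether the dependent variable is the change, the follow-up score or both time points. The analysis set consists of participants who completed the scale on both occasions.

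Protocol article, 'Randomisation': the strata are two practice-level factors, single or group practice and teaching or non-teaching practice. Practices are randomised after the baseline data are collected, so the baseline score cannot be affected by allocation.

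On planning: "power of (at least) 80% with a two-sided significance level α = 0.05", "assuming an intra-cluster correlation coefficient (ICC) of 0.05", and a "standard deviation for the primary endpoint of 73.6 ± 15 points".

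**The concern.** A change score subtracts the whole baseline value, which fixes the baseline slope at 1. With equal SDs at both times, the slope that minimises the variance is rho. For any rho below 1, subtraction therefore removes more baseline than it should and leaves avoidable noise in the effect estimate. It also over-corrects chance imbalance: a baseline difference D between arms moves the change-score estimate by (1 − rho)·D in the opposite direction.

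At stake are precision and the power claim. The SD of 15 is quoted alongside a mean score, so it describes a score at one time point and not a change. If rho is below 0.5, the change varies more than the planning SD allows. Every participant completes the baseline questionnaire, and the text as written does not use it in the most efficient way. The article fixes both the contrast and the adjustment terms, so this is a choice it makes and not a detail it merely leaves open.

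**Working it through.** **Inputs from 'Sample size calculation'.** Two-sided alpha 0.05; SD 15; ICC 0.05; K = 26 practices per arm; m = 3 staff per practice (4 and 5 as variants); difference 7.3 points. **Assumed, not in the article:** rho (shown as a range), equal SDs at baseline and follow-up, and ICC 0.05 for raw, change and baseline-adjusted scores alike.

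**Step 1: reproduce the plan's figures.** SE = SD × √(2 × [1 + (m − 1) × ICC] / (K × m)), with power from the noncentral t on 2(K − 1) = 50 degrees of freedom.

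- m = 3: design effect 1.10; SE = 15 × √(2.20/78) = 2.52; 7.3/2.52 = 2.90; power 81.1% (stated 81%).
- m = 4: design effect 1.15; SE = 15 × √(2.30/104) = 2.23; power 89.4% (stated 89%).
- Detectable difference at 80% power: 0.425 SD for m = 4 (stated 0.43) and 0.388 SD for m = 5 (stated 0.39).

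The sample size arithmetic is correct for an SD of 15.

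**Step 2: SD under each analysis.**

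- Change score: 15 × √(2(1 − rho)). This equals 15 only when rho = 0.5.
- Baseline-adjusted: 15 × √(1 − rho²).
- Variance ratio, adjusted to change: (1 − rho²) / (2(1 − rho)) = (1 + rho)/2, a saving of (1 − rho)/2.

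**Step 3: power for 7.3 points, K = 26, m = 3.**

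| rho | SD of change | SD adjusted | Variance saved | Power, change | Power, adjusted |
|---|---|---|---|---|---|
| 0.3 | 17.75 | 14.31 | 35% | 67.1% | 84.6% |
| 0.4 | 16.43 | 13.75 | 30% | 73.7% | 87.3% |
| 0.5 | 15.00 | 12.99 | 25% | 81.1% | 90.7% |
| 0.6 | 13.42 | 12.00 | 20% | 88.8% | 94.4% |
| 0.7 | 11.62 | 10.71 | 15% | 95.6% | 97.8% |
| 0.8 | 9.49 | 9.00 | 10% | 99.4% | 99.7% |

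**Step 4: larger practices and the smaller effect.**

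- m = 4, 7.3 points: rho 0.3, 77.4% by change score and 92.0% adjusted; rho 0.5, 89.4% and 96.0%.
- m = 5, 7.3 points: rho 0.3, 84.3% and 95.7%; rho 0.5, 94.0% and 98.2%.
- m = 4, 6 points (0.4 × 15, the minimally important difference the article cites): rho 0.3, 61% and 79%; rho 0.5, 75% and 86%; rho 0.6, 84% and 91%.

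**Step 5: chance imbalance.** With m = 3, the SE of the baseline difference between arms is also 2.52 points. A one-SE imbalance at rho 0.5 moves the change-score estimate by (1 − 0.5) × 2.52 = 1.26 points, against a target of 7.3. This is the same loss of precision seen from another side, not an additional one.

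**The case against.** **The model may already use baseline well.** The article does not call its two adjustment terms exhaustive, and the dependent variable is unstated. A mixed model on both time points with a common baseline mean would have about the precision of baseline adjustment, and a fuller document may specify one. This stands as a limit: it cannot be said that baseline is excluded. But the text states a contrast on change and names its adjustment terms, and an analyst following it literally would fit a change-score comparison.

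**The loss may be small.** This also stands. At rho 0.8 power is close to 100% either way. Three staff per practice is the smallest scenario. The workshop description expects 23 to 35 people from 5 or 6 practices, or about 4 (23/6) to 7 (35/5) per practice. At 5 per practice the change score exceeds 80% for 7.3 points even at rho 0.3. It does not do so for 6 points at that rho (68%). The ICC of a change score also need not be 0.05, because subtraction removes stable practice differences.

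**Three stronger readings that the article does not support.**

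- *That the planned contrast is biased or ignores baseline.* Baseline is measured before randomisation and is subtracted, so the comparison is valid.
- *That the sample size arithmetic is wrong.* It reproduces. What depends on rho is whether SD 15 suits a change score.
- *That leaving out staff role is an error.* The only support is this: "As the values and standard deviation are lower on this scale for physicians than for practice assistants". That concerns level and spread. A constant gap in level cancels in a change score, and no role difference in change is reported. Assuming one third physicians and rho 0.5, a gap of 5 points explains about 0.8% of the residual variance after baseline adjustment (2/9 × 2.5² / 168.75), and a gap of 10 points about 3.3%.

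**Conclusion.** The point holds as one of efficiency. The article sets the primary contrast on change, names clustering and strata as adjustment terms, and does not name an available pre-randomisation baseline score as a covariate. Followed literally, this gives up (1 − rho)/2 of the variance: 35% at rho 0.3, falling to 10% at rho 0.8.

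In power terms, the loss with 3 staff per practice and 7.3 points is about 18 percentage points at rho 0.3, 10 at rho 0.5 and 2 at rho 0.7. Below rho 0.5 the change-score analysis in that scenario falls short of the stated 81%, while the baseline-adjusted analysis stays above it at every rho examined.

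These figures rest on equal SDs at both times, ICC 0.05 on every scale and a rho that the article does not give. The repair is worth making because it needs no new data and, on these assumptions, is more precise at every rho below 1.

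**What to change.** State the primary model in full: follow-up job satisfaction regressed on arm, individual baseline score, single/group practice and teaching/non-teaching practice, with a random practice effect. A constrained-baseline repeated-measures mixed model is an acceptable alternative. Use the same form for the secondary scales measured at both times, and report change scores descriptively. The hypotheses in 'Sample size calculation' can then be restated as the adjusted between-arm difference at follow-up, which targets the same effect.

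Staff role and the practice-mean baseline score may be added as optional covariates if they are prespecified; nothing in the article makes them necessary.

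The cost is wording in the analysis plan, settled before follow-up data are analysed. The baseline score is already collected, and the sample size need not change.
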